**ENROLMENT**:								
**Eligibility screening**	X							
**Database preparation**	X							
**Informed consent**		X						
**Allocation**		X						
**INTERVENTIONS**:								
***[Experimental Intervention]***								
***[Control Intervention]***								
**ASSESSMENTS**:								
***[BASELINE ASSESSMENT]***		X						
***[FOLLOW-UP ASSESSMENT]***								X
***[FINAL ASSESSMENT]***								X
***DISSEMINATION OF RESULTS***:								X

#### Description of the variables

The main variable will be the degree of dependence in performing the activities of daily living (ADL), as measured using the Barthel Index. The secondary variables will be cancer-related asthenia, attention and cognitive functions, health-related quality of life (HRQoL), pain, functional capacity, fear/avoidance of movement using the Tampa Scale for Kinesiophobia associated with Fatigue (TSK-F), and body composition. We will also record the following intervening variables from the patient clinical history: pathological diagnosis, number of treatment lines, and other sociodemographic and anthropometric data.

#### Tools employed in the evaluation of the variables

“Barthel Index, (BI)” [21]: to evaluate dependence. Measures physical disability with proven validity and reliability. It is easy to apply and to interpret. Useful for evaluating the patient’s functional independence in the activities of daily living (ADL). Scored from 0 to 100, it quantifies the individual’s degree of dependence.“4th version of the Functional Evaluation of Cancer Therapy-Anaemia (FACT-An)” [22]: to evaluate cancer-related asthenia and the functional capacity. The FACT-An scale comprises the FACT-G fatigue subscale, plus seven non-fatigue items related to anaemia in cancer patients. In this study, we will use the version of FACT-G for cancer-related fatigue.“Trail-Making Test (TMT)” [23]: to evaluate attention and executive functions. Useful for to assess attention, flexibility of thinking, and visuospatial ability. The global TMT comprises two parts: the TMT A measures attention, and the TMT B assesses processing speed and executive functions.“EuroQol 5-D Questionnaire (EQ-5D)” [24]: to assess the health-related quality of life (HRQoL). It has been adapted and validated for use in the Spanish population.“A Visual Analogue Scale (VAS)” [25, 26], to evaluate the pain. This will be assessed using the VAS as the most widely used pain assessment scale pain intensity is represented on a 10 cm line where 0 indicates the absence of pain and 10 represents the worst pain imaginable. The patient indicates the intensity of their pain; values less than 4 mean mild or mild–moderate pain; 4–6 indicate moderate–severe pain; and greater than 6 implies very intense pain.“Short Physical Performance Battery (SPPB)” [27]: to evaluate Functional capacity. This test has been validated in the Spanish population for primary healthcare, and was specifically designed to predict disabilities, combines balance, gait speed, and the ability to get up from a chair and has been shown to predict adverse events, dependency, institutionalisation, and mortality.The “Tampa Scale of Kinesiophobia–Fatigue (TSK-F)” [18, 28], was developed to evaluate the fear of movement related to fatigue/pain. It has been proven effective in oncology patients and those with chronic fatigue syndrome. We will use the model with 11 items (TSK-F-11).Evaluation of body composition: by measuring the waist, hip, brachial, thigh, wrist, and ankle circumferences. Height and weight will be measured using a portable stadiometer (Seca, 222), calculating the average of two recorded measurements.

An individual data collection sheet will be used for each patient and recorded in a database specifically designed for this study.

#### Interventions

Conventional standard of care will be applied in both groups, explaining to each subject participating in the study the importance of compliance and adherence to the prescribed pharmacological treatment and the established guidelines personalised to their specific health needs. In the days prior to hospital discharge, they will also receive, as a part of the intervention, a health education programme with an informative talk and written guidelines, mainly focused at reinforcing and promoting an active and healthy lifestyle.

The difference of the intervention in the experimental group will be due to the fact that we will also implement the intervention with a multimodal programme of physical exercise and functional rehabilitation lasting one month. This will consist of:

1. A prescription for multimodal physical exercise. In the Oncology Hospitalisation Unit at the CAUSA, as in other studies already initiated [19], we will carry out the following design of a multimodal physical exercise programme. A supervised and structured program will be implemented in these patients for one month. This will consist of two short 15–20-minute sessions performed daily, one in the morning and one in the afternoon. The sessions will be structured according to the recommendations of the American College of Sports Medicine (ACSM) [29, 30], with an initial warm-up (2–3 min), the main section comprising the principal physical exercises (8–12 min), and a final cool-down and relaxation phase (5 min).

Parts of a standard session: The warm-up will consist of exercises designed to promote joint mobility and muscle activation. The main section will combine aerobic and balance exercises with low-load strength exercises targeting upper and lower quadrant muscle groups. The dosage and load will always be adapted according to patient evaluations performed beforehand and will follow a progression in difficulty with the aim of achieving an intensity at 50–75 % of each patient’s maximum heart rate or a perception of moderate effort on the Borg Scale. After 15 days of the program, the second evaluation will be carried out and the program may then be modified by adapting the load. Finally, the cool down will consist of gentle muscle stretching and relaxation exercises.

2. Activities of daily living re-education. Specific training designed to identify factors impeding the performance of the ADL will be conducted after the assessment and before the time of patient discharge from the hospital. This intervention will comprise three parts: (1) a direct ADL intervention carried out in situ in the hospital which will be generalisable to the patient’s everyday environment; (2) teaching of energy saving techniques (ESTs) based on the simplification of activities; and (3) advice on sleep hygiene measures for sleep disorders, as outlined in the specific NCCN guidelines on cancer-related asthenia [31].

3. Prescription of assistive products and environmental adaptations. Before the patient is discharged and after the baseline evaluation, we will evaluate if any support products that will favour their autonomy can be prescribed and at the time of hospital discharge and we will identify possible barriers in their home that could impair their autonomy.

#### Work plan and visit structure

Once the possible study candidates have been identified in the Oncology Hospitalisation Unit at the CAUSA, an interview with each individual will be organised to explain the purpose of the study to them and thereafter, invite them to sign the informed consent to their participation. Each participant will complete 3 planned evaluation visits. One at baseline, prior to randomisation, and two follow-up visits 15 days and 1 month after the first visit. The structure of all three 3 visits will be the same and each will last approximately one hour. In addition, there will be a telephone follow-up 3 and 6 months after the randomisation. The study variables will be evaluated during these visits, as specified in Table 1.

#### Baseline visit

This will be performed prior to patient discharge and ensuring compliance with the selection criteria. The evaluation will involve collection of all the study variables and completion of the questionnaires at baseline; the patient sociodemographic data, medical history, presence of comorbidities, and use of concomitant medications will also be recorded. At the end of this visit the patients will be randomly assigned to one of the two study groups. Participants included in the experimental group will then be explained the structure and organisation of the functional rehabilitation program during a specific visit planned for this purpose.

#### Follow-up visits at 15 days and 1 month

These visits will be identical to the baseline evaluation, except that the sociodemographic variables will only be collected at the baseline evaluation. The follow-up visits will be completed in the Clinical Teaching Assistance Unit in the Faculty of Psychology at the University of Salamanca, Spain.

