### Sample/participants

Participants: The patients will be recruited from the Oncology Hospitalisation Unit at the CAUSA when they will be hospitalised. The Unit’s investigators will invite patients to participate in the study by explaining the details of the clinical trial, and they can then be included once they have given their verbal and written consent, and meet the following selection criteria: (A) Inclusion criteria: Participants must have a pathological diagnosis of an oncological disease, be over 18 years of age, be hospitalised at the time of recruitment in the Oncology Hospitalisation Unit at the CAUSA, having a score of 15–55 points on the Barthel Index (BI), having a score of 4 or more on the visual-analogue scale (VAS) for cancer-related asthenia and have signed an informed consent form indicating voluntary agreement to participate in the study. (B) Exclusion criteria: not having an adequate cognitive state to be able to comprehend and follow the orders provided (fewer than 23 points on the Mini Mental State Examination, MMSE), and having a haemoglobin level lower than 10 g/dL. (C) Withdrawal criteria: disease progression which brings the patient to a terminal situation or to death, and non-completion of the follow-up and final assessments.

Assignment, randomisation and blinding: After recruitment, individuals will be assigned by a randomisation process to one of two study groups: Experimental Group or Control Group. Detailed in Fig. 1.

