### Procedures and data collection

#### Evaluations and study plan

Participants will be assessed at three points during the study: Firstly, the baseline assessment at the beginning, the second assessment after seven days, and a third final assessment, before the patients are discharged from hospital. The baseline assessment will be performed after recruitment and before randomisation and assignment of subjects to the corresponding group. This initial assessment includes the recording of the independent variables and the primary and secondary outcome variables of the study. Then, after randomisation, the corresponding intervention will begin to be applied to each group. Subsequently, the other further assessments will be carried out, one after seven days, considered as the follow-up assessment, and another at hospital discharge, considered as the final assessment. This can be seen in more detail in Table 1.

**Table 1 Tab1:** Timeline and dimensions assessed at the time points

	STUDY PERIOD							
	**Enrolment**	**Allocation**	**Post-allocation**					**Close-out**
**TIMEPOINT**	***Month 1-2***	***Month 2-3***	***M4***	***M5***	***M6***	***M7***	***M8***	***M9-M12***

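### Off-site visits at 15 days and 1 month put the Barthel Index at risk of being missing in patients who stay dependent, and a missed assessment is listed as a withdrawal

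*Protocol article*

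**What the plan says.** All places are in the protocol article.

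- **Entry (Sample/participants).** Patients must be hospitalised, with an asthenia score of at least 4 on the VAS and "having a score of 15–55 points on the Barthel Index (BI"). The index runs from 0 to 100.
- **Baseline (Baseline visit).** "This will be performed prior to patient discharge and ensuring compliance with the selection criteria".
- **Timing (Work plan and visit structure).** "One at baseline, prior to randomisation, and two follow-up visits 15 days and 1 month after the first visit". Each visit takes about an hour.
- **Place (Follow-up visits at 15 days and 1 month).** "The follow-up visits will be completed in the Clinical Teaching Assistance Unit in the Faculty of Psychology".
- **A different schedule (Evaluations and study plan).** Here the later assessments are "the second assessment after seven days, and a third final assessment, before the patients are discharged from hospital".
- **Telephone (Work plan and visit structure).** "there will be a telephone follow-up 3 and 6 months after the randomisation". What these calls collect is not separately defined.
- **Withdrawal (Sample/participants).** The criteria include "non-completion of the follow-up and final assessments".
- **Main variable (Description of the variables; Sample size).** The Barthel Index, which also carries the sample size: 25 per group, a 17-point difference in change, 90% power. No allowance for loss is stated.
- **Analysis (Data analysis).** Intention to treat, with a time-by-group repeated measures ANOVA.

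**The concern.** The main outcome measures dependence, and obtaining it at 15 days and 1 month requires a trip to a university building by people selected because they were dependent. Whether a Barthel score is observed may therefore depend on the score itself. The withdrawal criterion then turns a missed assessment into an exit from the study.

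Attendance may also differ between arms. Only the experimental arm has a month of supervised sessions, a review of assistive products and a check for barriers at home. These could make attendance easier, or leave a different kind of patient unable to attend.

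If loss depends on the unobserved score, a repeated measures ANOVA as usually run, on complete cases, does not correct it. No later analysis can do so without untestable assumptions. At 50 patients, a few selective losses matter. Much of the risk can be avoided at the point of collection, because the Barthel Index and the questionnaires can be taken by interview.

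**Working it through.** **1. The plan's own figure.** Inputs from Sample size: difference D = 17, n = 25 per group, two-sided alpha 0.05, stated power 90%. The same sentence gives a beta of 0.2, which is 80% power. No SD is stated, so the 90% cannot be reproduced. It can only be solved backwards for the SD:

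- 90% power needs an SD of 18.2 (noncentral t) or 18.5 (normal approximation).
- 80% power needs an SD of 21.0 (t) or 21.5 (normal).

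The rest assumes an SD of about 18 for the change in Barthel Index, the value that fits the stated 90%.

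**2. Random loss.** Power ≈ Φ(D / (SD·√(2/n)) − 1.96); the t column uses the noncentral t instead.

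| Loss per arm | n per arm | Power, t (SD 18.2) | Power, normal (SD 18.5) |
|---|---|---|---|
| 0% | 25 | 90% | 90% |
| 20% | 20 | 82% | 83% |
| 30% | 17.5 | 77% | 77% |

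**3. Hard truncation: every missing patient is among the lowest scorers.** If the lowest fraction p of a normal distribution is lost, the mean of the remainder rises by SD·φ(z_p)/(1 − p).

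- p = 0.15: 0.2332/0.85 = 0.274 SD.
- p = 0.30: 0.3477/0.70 = 0.497 SD.
- 15% in one arm and 30% in the other: (0.497 − 0.274) × 18.17 ≈ 4.0 points, about 24% of 17.
- 10% and 20%: (0.350 − 0.195) × 18.17 ≈ 2.8 points.
- 20% and 30%: (0.497 − 0.350) × 18.17 ≈ 2.7 points.
- Equal fractions in both arms: 0.

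The sign depends on which arm loses more. If it is the control arm, its mean is inflated and the difference shrinks. If it is the experimental arm, the difference is exaggerated.

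**4. Softer dependence.** The log-odds of a missing visit fall by 0.5 to 1.5 per SD of Barthel change, under the same rule in both arms. True difference 17, SD 18.54, completers only, numerical integration.

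| Overall loss | Slope | Loss, control / experimental | Observed difference | Power |
|---|---|---|---|---|
| 20% | 0.5 | 23% / 17% | 16.4 | 81% |
| 20% | 1.0 | 26% / 14% | 15.1 | 78% |
| 20% | 1.5 | 28% / 12% | 14.0 | 75% |
| 30% | 0.5 | 35% / 25% | 16.2 | 75% |
| 30% | 1.0 | 38% / 22% | 14.7 | 71% |
| 30% | 1.5 | 40% / 20% | 13.2 | 66% |

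At 20% loss the bias is 17 − 16.4 = 0.6 to 17 − 14.0 = 3.0 points, toward no effect. The direction follows from the assumption that one rule applies to both arms.

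**5. The two schedules side by side.** Evaluations and study plan has day 7 and a final assessment before discharge, so the final assessment needs no travel. Work plan and Follow-up visits have 15 days and 1 month, off site. The Interventions section also places the second evaluation after 15 days of the programme. The travel problem exists only if the off-site schedule governs.

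**The case against.** A reader might infer that the Barthel Index *will* be missing mainly in patients who do not recover. The article does not support that. It has no attendance, dropout or transport figures, and the 15–55 range describes patients in hospital at entry, not two or four weeks later. What it supports is a risk.

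The other counter-arguments, and what stands of each:

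- **The premise rests on one of two schedules.** This stands, and the schedules must be reconciled first. It does not dispose of the point, since three sections agree on day 15 and two of them on the 1-month visit.
- **The full protocol may arrange transport or home visits.** Possible, and silence on this is not itself the fault. But the place of the visits and the withdrawal criterion are stated, and together they create the risk.
- **The 4-point figure follows from the chosen loss rates.** True. It is zero with equal truncation, and the documents give neither the rates nor the arm that loses more. It is one end of a range, not an estimate.
- **The planned telephone calls are at 3 and 6 months.** True. They show that telephoning patients is within the plan, not that the Barthel Index is already planned by telephone.
- **A telephone fallback confounds mode with dependence, and an unblinded patient may reveal allocation.** Both are real costs, though disclosure can also happen in the clinic. Neither makes losing the outcome preferable. A clinic-only analysis cannot settle the mode question, because it is the complete-case analysis at issue.

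**Conclusion.** The point holds as a preventable risk to the main outcome, conditional on the off-site schedule being the one in force. The entry range, the place of the visits and the withdrawal criterion together allow loss that depends on the outcome and may differ by arm, and the withdrawal criterion sits badly with an intention-to-treat analysis.

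Size and direction are unknown. With an assumed SD of about 18, the bias lies between 0 and about 4 points under hard truncation at the rates tried, and at about 0.6 to 3 points under softer dependence at 20% overall loss. Random loss of 20–30% alone would take 90% power to about 82–77%. That last effect comes from having no allowance for loss, wherever the visits are held. The loss rates, slopes and SD are all assumptions. The change is worth making because it is cheap and an outcome not collected cannot be recovered.

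**What to change.** 1. Reconcile Evaluations and study plan with Interventions, Work plan and Follow-up visits, so that one timing and one place apply to each assessment.
2. If the off-site visits stand, add to Follow-up visits at 15 days and 1 month: *When a participant cannot attend within the visit window, the blinded assessor collects the Barthel Index, FACT, EQ-5D, pain VAS and TSK-F by telephone within that window, from the participant or, where applicable, a caregiver. The procedure is identical in both arms and the mode and respondent are recorded. SPPB, Trail-Making Test and body measurements are taken in person only.*
3. Amend the withdrawal criteria in Sample/participants so that a missed assessment is recorded as missing data and is not a withdrawal from follow-up or from the analysis.
4. Report mode of collection by arm, and examine it in a sensitivity analysis that accounts for mode. Show clinic-only results as descriptive support only.

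The cost is some calls by assessors already in place, one or two recorded fields and a short amendment. The downside is mixed mode of collection, with some added risk that patients disclose their group. The pain VAS, described as a 10 cm line, would need a spoken equivalent by telephone.

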### Data analysis

The statistical analysis will be carried out on an intention-to-treat basis. The characteristics of the population will be presented as means and standard deviations for continuous variables and as a frequency distribution for qualitative variables. To assess comparability of the two study groups at the baseline, the means between both groups will be compared using chi-square tests for qualitative variables and Student t-tests for qualitative variables. The effect of the intervention on the study variables will be evaluated using a repeated measures ANOVA with two study factors: time * group. Subgroup analyses will be carried out considering certain variables and/or categories from the baseline evaluation such as age or the initial FACT scale score. For hypothesis testing, an alpha risk of 0.05 will be set as the limit for tests of statistical significance. We will use SPSS software (version 23.0; IBM Corp., Armonk, NY) for all the statistical analyses.

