**Fig. 1 Fig1:**
[figure not shown]
Study design. The enrolled participants will be randomly assigned to one of the study groups and will be assessed at three pre-specified time p

We will employ a simple randomisation process that consists of generating a table of random numbers of the same size as the estimated study sample with Microsoft Excel 2020 to assign subjects to each of the study groups. For even numbers, the subject will be assigned to the Experimental Group, and for odd numbers, the subject will be assigned to the Control Group. Randomisation, recruitment and assignment of subjects to each group will be performed by research staff not involved in the evaluations or interventions in each group, which will avoid potential bias in the study.

The participating subjects will not be blinded, due to the specific characteristics of the intervention in each group. However, the researchers responsible for the study measurements and statistical analysis will be blinded, with the intention of avoiding any contamination between groups, thus increasing the rigour of the study process.

Sample size: The sample size has been estimated based on the potential modification of one of the main outcome of the study—the score on the Barthel Index. For this calculation, we have considered the results obtained in a similar, where a modification of 17 points in the BI score was obtained, as a difference attributable to the intervention, considering this as the difference between the modification of the experimental group and the control group [20]. With these premises, accepting an alpha risk of 0.05 and a beta risk of 0.2 in a bilateral contrast, with 50 individuals (25 subjects in the experimental group and 25 in the control group, the statistical power was 90 % to recognize as statistically significant a change of 17 points between both groups in the BI score. The sample size was estimated using the programme EPIDAT 4.2.

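### The trial is sized on one between-group difference in Barthel change, but the only efficacy test named is a time-by-group ANOVA, which with three assessments is a different, 2-df test

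*Protocol article*

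**What the plan says.** The sample size paragraph (under Sample/participants) takes its effect from a similar study, "where a modification of 17 points in the BI score was obtained, as a difference attributable to the intervention", and defines it by "considering this as the difference between the modification of the experimental group and the control group". The error rates are set by "accepting an alpha risk of 0.05 and a beta risk of 0.2 in a bilateral contrast". The trial is planned "with 50 individuals (25 subjects in the experimental group and 25 in the control group", and "the statistical power was 90 % to recognize as statistically significant" that 17-point change. No SD and no time point are given.

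Description of the variables makes the Barthel Index the main variable: "The main variable will be the degree of dependence in performing the activities of daily living (ADL), as measured using the Barthel Index".

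Data analysis states one method for the intervention effect, which "will be evaluated using a repeated measures ANOVA with two study factors: time * group", and adds that "an alpha risk of 0.05 will be set as the limit for tests of statistical significance". It does not say which term decides, which time levels enter, whether baseline is a covariate, or which visit counts.

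Three assessments, including one before randomisation, are planned in both descriptions of the schedule. Evaluations and study plan puts the later two at seven days and at hospital discharge. Work plan and visit structure, and the section on the follow-up visits, put them at 15 days and 1 month.

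**The concern.** A difference between arms in change from baseline is a 1-df contrast. A group-by-time interaction over three levels has 2 df and asks a different question: whether the two mean profiles differ in any way. Three things follow if that interaction is the efficacy test.

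- The stated 90% power does not describe the stated test.
- A significant result can come from a difference at the intermediate visit that has gone by the end.
- The test itself gives no estimate or confidence interval to compare with 17 points.

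Barthel at baseline is already collected, yet the stated method uses it as one of the outcomes and not as a covariate.

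**Working it through.** **Inputs from the protocol article.** Difference 17 points; 25 per arm; two-sided alpha 0.05; power 90%; three assessments including baseline; eligible baseline Barthel 15-55.

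**Assumed, because not given.** SD of change, correlation between visits, and the size of the effect at the mid visit.

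**1. The plan's own figure.** Without an SD the 90% cannot be reproduced, only inverted.
- Normal approximation: SD = 17 / [(1.960 + 1.282) × √(2/25)] = 17 / (3.242 × 0.2828) = 18.5.
- t-test with 48 df: SD = 18.17. The noncentrality is 17 / (18.17 × 0.2828) = 3.31 and the critical value 2.01.
- At SD 18.54, 80% power needs 2 × (18.54 × 2.802 / 17)² = 18.7, so 19 per arm, and 25 per arm gives 90%. Beta 0.2 and power 90% can therefore be a target and an achieved value.

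**2. Where the mismatch arises.** With two time levels, the interaction F equals the square of the change-score t, and sizing and analysis would agree. The third level breaks that equality.

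**3. Power of the 2-df interaction.** Under compound symmetry the within-subject error variance is SD²/2 = 18.17² / 2 = 165. For between-arm differences D at the three assessments, the noncentrality is λ = 25 × Σ(D − mean D)² / (2 × 165), with critical F(2, 96) = 3.09.

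| Difference at baseline, mid, last | Σ(D − mean D)² | λ | Power |
|---|---|---|---|
| 0, 8.5, 17 (linear) | 144.5 | 10.9 | 0.84 |
| 0, 17, 17 (early plateau) | 192.7 | 14.6 | 0.93 |
| 0, 0, 17 (late only) | 192.7 | 14.6 | 0.93 |
| 0, 17, 0 (mid visit only) | 192.7 | 14.6 | 0.93 |

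The change-score test at the last visit has power 0.90 in the top three rows. In the bottom row the interaction is significant 93% of the time although nothing remains at the last visit.

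**4. Baseline-adjusted last-visit contrast, equal SDs.** SD of change² = 2σ²(1 − ρ) and the ANCOVA error variance is σ²(1 − ρ²), so the ratio is (1 + ρ)/2.
- ρ = 0.3: ratio 0.65, power 0.98
- ρ = 0.5: ratio 0.75, power 0.96
- ρ = 0.7: ratio 0.85, power 0.94

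**5. The same contrast with a restricted baseline.** Scores confined to 15-55 cannot have a population SD above 40/2 = 20; a uniform spread gives 40/√12 = 11.5. Take 11. The follow-up SD s solves s² + 121 − 22rs = 18.17², and the ratio is s²(1 − r²) / 18.17².
- r = 0.3: s = 18.1, ratio 0.91, power 0.93
- r = 0.5: s = 21.0, ratio 1.00, power 0.90
- r = 0.7: s = 24.1, ratio 0.90, power 0.93

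The gain over the change score is then 0-3 percentage points.

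**6. Sensitivity.**
- With the SD that gives the change score 80% power (21.0), the linear interaction has 0.71 and the early-plateau interaction 0.84.
- Under AR(1) correlations of 0.7-0.9, the interaction has about 0.91-0.92 for a linear build-up and 0.97 for an early plateau or late-only effect, against 0.92-0.96 for ANCOVA.
- Simulation with 6,000 runs (compound symmetry, ρ = 0.5) gave 0.83 / 0.90 / 0.96 for interaction, change score and ANCOVA with linear build-up, and 0.93 / 0.90 / 0.96 with early plateau.

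**The case against.** **The term tested is not spelled out.** The article does not call the interaction an omnibus test or say that baseline is a time level, and contrasts and covariates are often left to an analysis plan that is not shown. This stands as a limit on wording: the 2-df interaction is the natural reading, not a quotation. It does not remove the point, because the article does state its method and, separately, the contrast it was sized on, and with three assessments the two differ.

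**The method is valid.** A time-by-group ANOVA is a randomised comparison at the stated alpha. Preferring a baseline-adjusted contrast is an argument about target and efficiency, not about bias. This stands.

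**Stronger readings that the article does not support.**
- A reader might infer that the planned test always loses power. It does not: with an early-plateau or late-only effect it beats the change score, and under AR(1) correlations, or with a baseline SD of 11, it can match or beat ANCOVA.
- A reader might infer that the 15-55 entry range makes baseline adjustment especially valuable. Step 5 shows the reverse tendency. Moreover, the equal-SD case at ρ = 0.7 needs a baseline SD of 18.17 / √0.6 = 23.5, above the cap of 20.
- A reader might count the 3- and 6-month telephone contacts as further time levels and so reach 4 df. Work plan and visit structure lists them apart from the three evaluation visits, and nothing puts them in the ANOVA.

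**Conclusion.** The mismatch between sizing and analysis holds. The 90% power belongs to a 1-df difference in Barthel change. The named analysis, read naturally, is a 2-df interaction that can respond to the intermediate visit alone and gives no single effect estimate. That conclusion needs only the three planned assessments and the absence of a named contrast.

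The power consequence is conditional. For a gradual build-up under compound symmetry with SD of change about 18.2, power is about 0.84, against 0.90 for the change score and 0.94-0.98 for a baseline-adjusted last-visit contrast (ρ 0.3-0.7, equal SDs). For an effect fully present at the mid visit, or only at the last, it is about 0.93. With a baseline SD near 11 the adjusted contrast has 0.90-0.93. Every SD, correlation and time course here is an assumption, because the article gives none. That the power of the stated test turns on an unknown time course is itself a reason to fix one contrast in advance. The plan should be changed on this point, but the ANOVA is not invalid.

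**What to change.** Reconcile the schedule before anything else: the final assessment is at hospital discharge in Evaluations and study plan and at 1 month in Work plan and visit structure and in the follow-up visits section. A primary contrast cannot be fixed until one time is settled.

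Then state in Data analysis that the primary analysis is the experimental-minus-control difference in Barthel Index at that one time point, with 95% CI, adjusted for baseline Barthel. Either an ANCOVA or that contrast from a mixed model with baseline as a covariate will do. Keep the time-by-group pattern as description.

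In the sample size paragraph, name the same contrast and time point, and give the SD (and correlation, if used) behind the 90%.

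The cost is a change of wording. It needs no new data, visits or patients, since Barthel is already measured at baseline.
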